### Possible negative effects of giving T4

Thyroxine is infrequently given to extremely premature babies. The only adverse effect that might be predicted is based on clinical experience of giving the drug to more mature patients, namely a persistent tachycardia. The drug may increase metabolic rate. In the critical paper by van Wassanaer et al[8], there was no difference in neurodevelopmental outcome as a result of T4 supplementation. However, a *post hoc *subgroup analysis showed that more mature babies who were given T4 supplementation had a worse neurodevelopmental outcome than those who were unsupplemented. The mechanism for this possible effect is not known.

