### Randomisation

Once all inclusion and exclusion criteria are met and informed consent has been obtained, infants will be included in the study and allocated a randomisation number. The randomisation lists will be computer generated with random variable block lengths using the statistical package STATA. The randomisation list will be stratified by centre, and gestational age at birth (under 25 weeks' gestation, 25–26 weeks' gestation, 27–27^+6 ^weeks' gestation). Multiple births will follow the randomisation process as per singleton births: each sibling in a multiple birth will receive the same treatment allocation.

Concealment of allocation will be provided by pharmacy departments of the respective hospitals. The randomisation list will be stored in a locked filing cabinet in the pharmacy Departments of each hospital and access will be limited to the pharmacist involved in the study.

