#### Blinding and Unblinding

Parents, investigators, clinicians involved in patient care and individuals assessing and analysing study end-points will all be blinded to the allocated study treatments. Levothyroxine and its placebo will be presented identically (see below). In the event that unblinding is necessary, there will be 24 hour access for unblinding and an Unblinding Case Report Form will be completed. In most cases, stopping the 'treatment' should be sufficient without the need for unblinding. Before unblinding is done, the case will be discussed with the Chief Investigator or in his absence a delegated member of the Trial Management Group.

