### Suspected Unexpected Serious Adverse Reactions

Given the vulnerability of these infants, the Chief Investigator and the Principal Investigators will review all serious adverse events in order to detect Suspected Unexpected Serious Reactions (SUSARs), involving other members of the Trial Management Group as appropriate. The procedure for identifying and reporting Suspected Unexpected Serious Adverse Reactions will be as follows.

All deaths or overdoses will be reviewed by the Chief Investigator (CI) or in his absence another member of the Trial Management Group. For each death the CI, or his deputy, will make a judgement about whether the nature or severity of the circumstances surrounding the death is consistent with adverse drug reactions associated with levothyroxine. Other members of the Trial Management Group who are available at the time may contribute to a discussion prior to the judgement. The judgement will take place within 24 hours of the notification of a death. If the nature or severity of the events leading up to the death are considered to be related to the study medication but inconsistent with what is known about levothyroxine, the allocation concealment for the affected infant will be broken by the sponsor. In the event of a death occurring in association with events that are not consistent with the information contained in this protocol and the infant was allocated to levothyroxine, the event will be labelled as a Suspected Unexpected Serious Adverse Reaction (SUSAR). If an overdose is thought to have led to a serious adverse event not listed in section 5.2 then the event will be labelled as a SUSAR. All events labelled as SUSARs will be reported to the sponsor within 24 hours of the decision being made. All SUSARs will be reported to the competent regulatory authority (MHRA) with a copy to the Sponsor as soon as possible but not later than 7 working days.

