The Trial Management Group will meet monthly in order to review all other Serious Adverse Events. The Group will consider whether each SAE is consistent with the information contained in this protocol about the nature and severity of adverse drug reactions associated with levothyroxine (including literature cited in the protocol). The CI or his deputy will make a judgement about whether the nature or severity of the circumstances surrounding the death is consistent with the information contained in this protocol about the nature and severity of adverse drug reactions associated with levothyroxine. If the nature or severity of the SAE is judged to be inconsistent with the information contained in this protocol the allocation concealment for the affected infant will be broken. In the event that a SAE occurs in association with events that are not consistent with the information contained in this protocol and the infant was allocated to levothyroxine, the event will be labelled as a Suspected Unexpected Serious Adverse Reaction (SUSAR) and reported as above.

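### The paragraphs on serious adverse events set different conditions for breaking an infant's allocation, and the rule for events other than deaths and overdoses omits relatedness

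*Protocol article*

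**What the plan says.** Four parts of the protocol article bear on this.

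- **Suspected Unexpected Serious Adverse Reactions, paragraph on deaths and overdoses.** After a death, the code is broken if the events leading up to it are "considered to be related to the study medication but inconsistent with what is known about levothyroxine". In that case "the allocation concealment for the affected infant will be broken by the sponsor".
- **Same section, paragraph on monthly review.** "The Trial Management Group will meet monthly in order to review all other Serious Adverse Events". The benchmark is the protocol's information "about the nature and severity of adverse drug reactions associated with levothyroxine (including literature cited in the protocol"). The rule is that where "the SAE is judged to be inconsistent with the information contained in this protocol the allocation concealment for the affected infant will be broken". If the infant turns out to be on levothyroxine, the event is labelled a SUSAR and reported in the way set out for deaths, which means to the sponsor within 24 hours of the decision.
- **Reporting Serious Adverse Events.** Investigators review all adverse events monthly for a suspected causal link. The SUSAR procedure follows if there is evidence that a new causal link may exist.
- **Blinding and Unblinding.** "Parents, investigators, clinicians involved in patient care and individuals assessing and analysing study end-points will all be blinded" to treatment. The section adds that stopping treatment will usually make unblinding unnecessary, and that a case is discussed before the code is opened.

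Two other statements matter. On levothyroxine's own reactions, Possible negative effects of giving T4 states: "The only adverse effect that might be predicted is based on clinical experience of giving the drug to more mature patients, namely a persistent tachycardia"; it adds that metabolic rate may rise. Under Randomisation, "each sibling in a multiple birth will receive the same treatment allocation".

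**The concern.** An event is normally unblinded for expedited reporting when it is both suspected to be caused by the drug and unexpected. The monthly-review rule keeps only the second condition. In infants born before 28 weeks, many serious events have nothing to do with the study drug and do not resemble a thyroxine reaction. Such an event can fail a consistency test without anyone suspecting levothyroxine, and the rule is mandatory once the test fails.

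At stake is the blind of the people who review later events and run the trial. Siblings share an allocation, so one opened code can disclose another infant's treatment while that infant is still being dosed and measured. In addition, an unrelated event would carry a SUSAR label in a levothyroxine infant, while the same event in a placebo infant would not.

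**Working it through.** The plan states no figure on this point, so the check is mainly a comparison of texts.

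**1. The three conditions side by side**

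| Source | Events covered | Condition | Who breaks the code |
|---|---|---|---|
| SUSAR section, deaths | Deaths | Related and inconsistent with what is known of the drug | Sponsor |
| SUSAR section, monthly review | All SAEs other than deaths and overdoses | Inconsistent only | Not stated |
| Reporting Serious Adverse Events | All adverse events | Evidence of a possible new causal link (entry to the SUSAR procedure) | Not stated |

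The less serious class of event therefore has the looser trigger. The monthly-review paragraph also still refers to the circumstances of the death although it covers other events, which suggests text carried over and incompletely edited.

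**2. Does the causality review act as a gate?** It is described as one way into the SUSAR procedure. The monthly-review paragraph has the group consider each SAE, and does not limit this to events already suspected to be causal. The document does not say which step comes first.

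**3. A worked case.** The Background names sepsis among the hazards for these infants. It is not in Table 1. Under Definitions, an event that prolongs hospitalisation is serious. An episode of sepsis that prolongs the stay is therefore an SAE, is not a listed expected event, and is not among the levothyroxine reactions that the protocol names. The sentence as written requires the code to be broken, whatever anyone thinks of causation.

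**4. Who could learn the allocation?** The SUSAR label applies only if the infant was on levothyroxine. Labelled events are then reported to the sponsor. The label thus comes before the report, so whoever applies it on the reviewing side would need the allocation. A broken code followed by a label points to levothyroxine, and one without a label points to placebo. This is an inference from the order of steps; no sentence says that the group receives the code.

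**5. Can the number of infants be sized?** For Table 1 events the answer depends on the reading.

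- *Table 1 counts as protocol information, or the causality review comes first:* about 0 infants from listed events.
- *Benchmark is levothyroxine reactions only, with Table 1 and the causality review set aside:* take the seven listed events other than death and tachycardia, with incidences 15%, 15%, 55%, 25%, 5%, 5% and 10%, and 150 infants (Sample Size Calculation). The lower bound is the largest single rate, 0.55 × 150 = 82.5. Under independence, 1 − 0.85 × 0.85 × 0.45 × 0.75 × 0.95 × 0.95 × 0.90 = 1 − 0.198 = 0.802, or about 120 infants. The rates sum to 1.30, so the upper bound is all 150.

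The range from about 0 to 150 shows that the wording does not settle the matter. For unlisted SAEs the protocol gives no incidence, so no count can be derived.

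**The case against.** The strongest reply is that the procedure as a whole does test relatedness. All adverse events are reviewed monthly for causality, the definition of an adverse reaction requires a relation to a dose given, and the stated purpose of the SAE review is to detect suspected reactions. A sensible investigator would not unblind for sepsis that nobody attributes to the drug. This stands to the extent that the protocol cannot be said to lack a relatedness test. It does not remove the contradiction, because the mandatory sentence does not refer to that test.

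A reader might also infer that routine complications of prematurity would unblind most of the trial. The documents do not support that. Table 1 lists those complications as expected, it is itself part of the protocol's information, and the Data Monitoring and Ethics Committee section monitors expected events across both groups, which would make little sense if each one opened a code. The 82 to 120 infants above belong to a reading that makes the expected-event list pointless, and independence is doubtful for complications of one condition.

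Nor does the document state that investigators will be unblinded. For deaths the sponsor breaks the code, and the monthly-review paragraph names no recipient. Disclosure to the reviewing group is a risk created by the order of labelling and reporting. Nothing extends it to outcome assessors or all treating clinicians.

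The safety comparison between arms does not rest on SUSAR labels either, since all adverse events are recorded on case report forms whatever their cause. The uneven labelling affects expedited reporting.

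The deaths paragraph is not perfectly drafted: its labelling sentence also leaves out relatedness, although its code-breaking sentence does not. Finally, the article refers to a Trial Standard Operating Procedure for reporting detail. Who is told the result may be settled there, so silence on that alone would not be a finding. The differing triggers are stated in the article itself.

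**Conclusion.** The point holds as a contradiction in a mandatory rule. Three places give three conditions for unblinding after an SAE, and the one for events other than deaths and overdoses omits relatedness and the code-breaker. Followed as written, it would break the blind for an unlisted SAE that nobody attributes to the drug, attach a SUSAR label if the infant is on levothyroxine, and could reveal the allocation of that infant and any sibling to the reviewing group. That conflicts with the blinding section.

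The size is indeterminate: about zero for Table 1 events if they count as protocol information, and unknown for unlisted SAEs. The conclusion rests on taking the monthly-review sentence literally and on the causality review not being a stated precondition for it. Disclosure to the group also rests on the label being applied before the sponsor is told.

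**What to change.** Reconcile the monthly-review paragraph with the deaths paragraph and with Reporting Serious Adverse Events:

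- Break the code only when an SAE has been judged, blind, to be both reasonably suspected as related to study medication and unexpected against Table 1 and the stated levothyroxine reactions.
- Have the Chief Investigator and Trial Management Group pass that blinded judgement to the sponsor. The sponsor breaks the code, applies the SUSAR label and makes the report.
- State that the allocation is not returned to the Chief Investigator, the group or the site unless it is needed for that infant's care.
- Remove the reference to a death from the paragraph on other events, and align the labelling sentence for deaths with its code-breaking sentence.

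The cost is wording in two paragraphs. The deaths paragraph already gives the sponsor the code-breaking role, and no infants or assessments are added. The small downside is that the Chief Investigator does not learn whether a reported event occurred on active drug.

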## Trial Oversight

### Data Monitoring and Ethics Committee (DMEC)

An independent Data Monitoring and Ethics Committee (DMEC) has been formed. During the period of recruitment, interim summaries of results will be supplied, in strictest confidence, to the DMEC by the trial statistician. At its first meeting the DMEC will determine the frequency of its meetings and the data to be supplied for the meetings. Meetings of the full committee will be arranged periodically as agreed by the full DMEC at the first meeting. In the light of interim data and emerging evidence from other studies, the DMEC will inform the Trial Steering Committee if, in their view, there is proof beyond reasonable doubt that the data indicate that any part of the protocol is indicated or contra-indicated either for all infants or for a particular subgroup of trial participants.

The decision to inform the steering committee will be, in part, based on statistical considerations. Appropriate criteria for the 'proof beyond reasonable doubt' cannot be specified precisely, but a difference of at least 3 standard deviations of a major endpoint may be needed to justify halting or modifying the study prematurely. If a 2–5 fold increase, depending on the event, is seen in any of the expected serious adverse events across both groups, then an emergency DMEC meeting will be called. However, discretion will used around the cut-off points based on discussion with the Trial Management Group members.

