## Statistical Consideration

### Sample Size Calculation

A sample size of 64 in each group will have 80% power to detect a difference between the means of the thyroxine and placebo groups of 0.67 mm (0.5*SD) for the outcome subarachnoid space at 36 weeks' CGA. This assumes that the common standard deviation is 1.3 mm and analysis is based on using a two group t-test with a 0.05 two-sided significance level. The value for the SD is taken from Armstrong et al[54] who report subarachnoid space as an indirect method of brain growth in preterm infants.

To ensure the appropriateness of the SD used in our calculations we will run an internal pilot after the first 30 infants have been randomised. We will compare the SD of these 30 infants with the standard deviation of Armstrong et al[54]. An internal pilot[49] can be used to increase but not decrease the size of the study. Assuming the 20% loss to follow up that we have experienced in an ongoing trial on the unit, we aim to recruit and randomise 150 infants with gestation below 28 weeks'.

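### The DMEC's only numeric guide to a halting difference is set in standard deviations of an endpoint, about six times the planned effect, and so gives no usable benchmark

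*Protocol article*

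**What the plan says.** The DMEC section of the protocol article states that "The decision to inform the steering committee will be, in part, based on statistical considerations" and that "Appropriate criteria for the 'proof beyond reasonable doubt' cannot be specified precisely". It then gives one figure: "a difference of at least 3 standard deviations of a major endpoint may be needed to justify halting or modifying the study prematurely". It names no standard error, test statistic or p-value.

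The next sentence is a separate safety trigger. "If a 2–5 fold increase, depending on the event, is seen in any of the expected serious adverse events across both groups", an emergency DMEC meeting is called, with discretion around the cut-offs.

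The Sample Size Calculation section uses the same term for the spread between infants: "This assumes that the common standard deviation is 1.3 mm". It sets the target difference at 0.67 mm, labelled as half an SD, and states that "A sample size of 64 in each group will have 80% power" for a "two group t-test with a 0.05 two-sided significance level". Mortality is a listed secondary outcome, and Table 1 puts the expected death rate at 20%.

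**The concern.** A monitoring guide tells the committee roughly how strong the evidence must be before early action is considered. That strength is normally measured against the uncertainty of the estimated difference, which shrinks as infants accrue. A multiple of the endpoint's own SD measures the size of the effect instead and does not shrink. The article uses SD in that second sense when it sets the sample size. On a consistent reading, the guide asks for an effect several times larger than the trial was designed to find, whatever the number of infants.

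At stake is whether the DMEC has a meaningful benchmark for a between-arm difference, in either direction, in a very vulnerable population.

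**Working it through.** **Inputs.** SD 1.3 mm, target 0.67 mm (0.5 SD), 64 per arm, 80% power and two-sided 5% level (Sample Size Calculation); death 20% and other event rates from 5% to 55% (Table 1). The look sizes of 30 and 32 per arm are my assumptions (32 is half of 64), because the article gives no look schedule. Formulas use a normal approximation with known SD and treat infants as independent, although siblings share an allocation.

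**1. The plan's own figure.** With 0.5 SD, n per arm = 2 × (1.960 + 0.842)² / 0.5² = 62.8, so 63. The exact t-test gives 63.8, so 64, with 80.1% power. The stated 64 is reproduced, and it rests on SD as between-infant spread. (With 0.67 mm and SD 1.3 mm taken literally, the t-test needs 61 and 64 gives 82.5% power.)

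**2. The guide in that unit.** 3 × 1.3 = 3.9 mm. 3.9 / 0.65 = 6.0 and 3.9 / 0.67 = 5.8.

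**3. On the z scale.** The standard error (SE) of the difference is 1.3 × √(2/n), so a 3-SD difference has z = 3 / √(2/n).

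| n per arm | SE (mm) | z of a 3-SD difference | 3 SE (mm) | Chance of reaching 3 SE if true effect is 0.67 mm |
|---|---|---|---|---|
| 32 | 0.325 | 12.0 | 0.98 | 17% |
| 60 | 0.237 | 16.4 | 0.71 | 43% |
| 64 | 0.230 | 17.0 | 0.69 | 47% |

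The two readings coincide only at 2 infants per arm, where 3 / √(2/2) = 3.

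**4. Chance of observing 3.9 mm.** With a true 0.67 mm and 32 per arm: (3.9 − 0.67) / 0.325 = 9.9, a probability of about 1e-23. With a true effect of 1 SD (1.3 mm, twice the planned 0.5 SD) and 30 per arm, SE = 0.336 mm and (3.9 − 1.3) / 0.336 = 7.7, a probability below 1e-13.

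**5. Mortality at 20%.** SD = √(0.2 × 0.8) = 0.40, so 3 SD = 120 percentage points. The largest possible difference from 20% is 80 points. Other definitions of the SD do not rescue it: with one arm at 20%, the largest possible difference is 1.63 SD on the pooled-sample SD and 2.83 SD on the average within-arm SD.

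**6. Other binary events.** On the pooled-sample SD the ratio can never exceed 2. On the control-arm SD, 3 SD is impossible at 15%, 25% and 55%, but arithmetically possible at 5% (5% to 70%) and at 10% (10% to 100%).

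**7. The safety trigger as a substitute.** If it is read on the pooled rate, control mortality of 20% and 40% on levothyroxine give a pooled 30%, a 1.5-fold rise. A 2-fold pooled rise (40%) needs 60% mortality on levothyroxine. It therefore does not serve as a guide to a between-arm difference.

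**8. The corrected scale.** At 30 per arm, 3 SE = 3 × 1.3 × √(2/30) = 1.01 mm, with an 81% chance of crossing under a true 1-SD effect. For mortality at 20%, 3 SE = 3 × 0.40 × √(2/n), which is 30 points at 32 per arm and 21 points at 64.

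**The case against.** The strongest reply is that the guide is soft. It says such a difference may be needed, that criteria cannot be precise, and that statistics are only part of the decision. The DMEC also weighs outside evidence. Other routes exist as well: deaths go to the Chief Investigator within 24 hours and are reviewed by the DMEC at regular intervals, each death is judged against known drug reactions, other serious events are reviewed monthly, and the fold-increase trigger calls an emergency meeting. A reader might infer that the DMEC is prevented from acting on excess deaths. The article does not support that, because nothing makes 3 SD a necessary condition. This part of the reply stands.

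It does not rescue the number. The other routes are case reviews and a meeting trigger across both groups, and none is a comparative halting criterion.

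A second reply is that the SD of an estimated difference is its standard error, so a trial statistician might apply the guide as |z| of 3 or more. That is probably what was meant. But the phrase ties the SD to an endpoint, and no other place in the article says that standard errors are intended.

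A third reply is that z = 3 is still demanding for mortality (about 30 points at 32 per arm). That is true: the corrected guide is strict but attainable, and the DMEC's judgement still has to cover smaller differences.

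**Conclusion.** The guide is wrong as written. In the article's own unit it is 3.9 mm, 5.8 to 6 times the planned effect, with z of about 12 at 32 per arm and 17 at 64. It is practically unreachable on the primary outcome and impossible for mortality at the expected 20%.

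Two stronger readings do not hold. One is that the threshold can never be met: on a continuous outcome it is extremely improbable, not impossible. The other is that it is impossible for every binary endpoint: at event rates of 5% to 10% it can be reached on a control-arm SD, though only through absurd differences.

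The conclusion rests on reading SD as the sample size section does. If standard errors were meant, the fault is one of wording and the remedy is the same. Because the guide is advisory and safety review continues by other routes, this is a should-fix.

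**What to change.** In the DMEC section, and in the DMEC charter if it repeats the phrase, replace the 3-standard-deviation wording with: *a difference of at least 3 standard errors of the between-arm difference (|z| ≥ 3, nominal two-sided p of about 0.0027) in a major endpoint*. Keep the existing wording that such a difference may be needed and that discretion applies.

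The change costs one phrase and does not alter the sample size. The downside is a small use of the 5% level at each look. By a simple upper bound, k looks at p = 0.0027 add at most k × 0.0027 to the type I error, for example 3 × 0.0027 = 0.0081 for an assumed three looks. The actual size depends on the number of looks, which the article leaves to the DMEC's first meeting.

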### Expected Serious Adverse Events

Extremely premature babies below 28 weeks' gestation constitute a high risk population: the following are serious adverse events and incidence rates which could be reasonably expected for this group of babies during the course of the study (Table 1).

**Table 1 T1:** List of Expected Serious Adverse events

Adverse event	Estimated incidence
a) death	20%*
b) necrotising enterocolitis or focal intestinal perforation diagnosed on clinical grounds, or at surgery	15%*
c) intracranial abnormality (parenchymal haemorrhage or focal white matter damage) on cranial ultrasound	15%*
d) requirement for supplementary oxygen 28 days after birth	55%*
e) patent ductus arteriosus requiring medical or surgical management	25%*
f) retinal surgery for retinopathy of prematurity	5%*
g) sustained tachycardia (greater than 220 beats per minute for more than 30 minutes in a 60 minute period)	20%**
h) pulmonary haemorrhage	5%**
i) persistent weight loss after 14 days after birth in the absence of infection.	10%**

* based on incidence of these complications at Liverpool Women's Hospital

** based on incidences estimated by the investigators

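### The emergency DMEC trigger cannot fire for oxygen at 28 days, and as a pooled rule it is insensitive to a rise in serious adverse events confined to the levothyroxine arm

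*Protocol article*

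**What the plan says.** Under Data Monitoring and Ethics Committee (DMEC), the protocol article sets one rule for an unscheduled safety meeting. Its condition is "If a 2–5 fold increase, depending on the event, is seen in any of the expected serious adverse events across both groups". Meeting that condition convenes the committee as an emergency. The next sentence softens the rule: "discretion will used around the cut-off points based on discussion with the Trial Management Group members".

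The same section gives the committee its own information: "interim summaries of results will be supplied, in strictest confidence, to the DMEC by the trial statistician". The committee decides at its first meeting how often it meets and what data it receives. The only other numerical criterion there concerns early halting or modification: "a difference of at least 3 standard deviations of a major endpoint may be needed to justify halting or modifying the study prematurely".

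Table 1 (Expected Serious Adverse Events) lists nine events with estimated incidences: death 20%, necrotising enterocolitis or focal perforation 15%, intracranial abnormality 15%, "requirement for supplementary oxygen 28 days after birth" 55%, patent ductus arteriosus (PDA) 25%, retinal surgery 5%, sustained tachycardia 20%, pulmonary haemorrhage 5% and persistent weight loss 10%. The article does not say which fold between 2 and 5 applies to which event.

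**The concern.** There are two difficulties, both visible from the protocol's own figures.

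First, a multiple of a baseline rate has a ceiling, because no rate can exceed 100%. The rule covers every event in Table 1, and some of those events are common. For at least one of them the lowest multiple in the range already exceeds the ceiling.

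Second, the count is taken across both groups. If levothyroxine raises an event rate and placebo does not, the placebo infants dilute the rise. The section Possible negative effects of giving T4 names persistent tachycardia as the one adverse effect to be predicted, and an effect of that kind would appear in the treated arm only.

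At stake is the speed of response. A rise in deaths or another listed event on levothyroxine would probably not call the emergency meeting and would wait for the next scheduled review.

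**Working it through.** **Inputs.** Event rates p come from Table 1. The fold range 2–5 comes from the DMEC section. Arm sizes come from Sample Size Calculation: 150 randomised, with equal groups (64 per group in the power statement), so 75 per arm at full recruitment. A look at 30 per arm is my assumption, to show an earlier point. The protocol gives no derivation or operating characteristics for the trigger, so there is no figure of its own to reproduce.

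**Step 1: ceiling on the fold.** The largest possible rise is 1/p.
- Oxygen at 28 days: 1/0.55 = 1.82, and 2 × 55% = 110%. No value in the 2–5 range can be reached.
- PDA: 1/0.25 = 4; 5 × 25% = 125%. Folds up to 4 can be reached.
- Death and tachycardia: 1/0.20 = 5; 5 × 20% = 100%, meaning every infant. Lower folds can be reached.
- The 15%, 10% and 5% events: 1/p is 6.67, 10 and 20. The whole range can be reached.

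**Step 2: dilution by pooling.** With equal arms, placebo at p and levothyroxine at 2p, the pooled rate is (p + 2p)/2 = 1.5p, below the lowest trigger. For a pooled doubling, (p + q)/2 = 2p gives q = 3p: levothyroxine must triple the rate.

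**Step 3: chance of firing when levothyroxine doubles the rate.** The pooled count is the sum of Binomial(n, p) and Binomial(n, 2p). The trigger, at its most sensitive fold of 2, needs at least 2p × 2n events. For death:
- n = 30 per arm: 24 of 60 needed, 6 + 12 = 18 expected; exact probability 5.9%.
- n = 75 per arm: 60 of 150 needed, 15 + 30 = 45 expected; exact probability 0.5%.

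A comparison between arms (pooled-variance z for two proportions, z ≥ 2 in the harmful direction) would flag the same doubling of deaths in 39% and 76% of trials.

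All events at 75 per arm:

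| Event | p | Levothyroxine rate needed for pooled 2-fold (3p) | Pooled 2-fold fires if levothyroxine doubles p |
|---|---|---|---|
| Death; tachycardia | 20% | 60% | 0.5% |
| PDA | 25% | 75% | 0.1% |
| Enterocolitis; intracranial abnormality | 15% | 45% | 1.9% |
| Weight loss | 10% | 30% | 5.7% |
| Retinal surgery; pulmonary haemorrhage | 5% | 15% | 15.5% |
| Oxygen at 28 days | 55% | impossible (165%) | 0% |

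For oxygen a doubling cannot occur even in one arm. If every levothyroxine infant were affected, the pooled rise would be (55 + 100)/2 ÷ 55 = 1.41-fold.

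**Step 4: where the pooled rule does better.** For a 5% event at 30 per arm the pooled rule needs 6 of 60. If levothyroxine doubles the rate, it fires in 29% of trials, against 10% for z ≥ 2. Part of that gain is a looser false-alarm rate: with no drug effect, P(Binomial(60, 0.05) ≥ 6) = 7.9%, against 1.4% for z ≥ 2.

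**Step 5: false alarms of an arm comparison.** With no drug effect, z ≥ 2 is reached in about 1.4–2.7% of trials per event per look. Over nine independent events, 1 − ∏(1 − aᵢ), where aᵢ is the false-alarm rate of event i, gives 18.9% at 30 per arm and 18.4% at 75 per arm.

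**The case against.** The strongest reply is that this trigger is only one layer of monitoring. The DMEC receives confidential interim summaries, sets its own data and timetable, and reviews deaths at regular intervals (Reporting Serious Adverse Events). The cut-offs are open to discretion. Investigators and clinicians are blinded, so a pooled rate is what they can see, and a pooled rule that alerts the DMEC is a coherent complement to its own review. By-arm tables usually belong in a DMEC charter, which is not shown.

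Much of this stands. A reader might infer that harm confined to one arm would go unmonitored; the document does not support that, because scheduled review continues. A reader might also infer that the thresholds for PDA, death and tachycardia are impossible. That would require attaching the top multiple to common events, whereas the fold is said to depend on the event and is not assigned. Only oxygen is out of reach over the whole range. Nor does the protocol say that the trigger was designed to detect an effect in one arm.

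Two things are left. The oxygen threshold contradicts Table 1 whatever fold is chosen. And the discretion clause is a weak remedy for dilution, since it is exercised in discussion with the Trial Management Group, while investigators are blinded and cannot see an imbalance between arms. Case-by-case review does not fill the gap either, because an excess of events that are individually expected shows only when rates are compared.

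**Conclusion.** The concern holds, at moderate severity. The emergency trigger cannot fire for one of its nine listed events, and as a pooled rule it would rarely respond to a doubling on levothyroxine alone: for death, about 6% of trials at 30 per arm and 0.5% at 75 per arm. It is a badly set rule within a monitoring scheme that otherwise exists, and it does not touch the primary analysis or the sample size.

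The figures assume that the increase is measured against Table 1, that the phrase about both groups means a pooled count, that allocation is equal, that placebo runs at the Table 1 rate, and that infants are independent. The first two are the natural readings but are not spelled out. Siblings share an allocation (Randomisation), so the probabilities are approximate. The oxygen result needs only the first assumption.

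**What to change.** Restate the pooled trigger as an absolute percentage for each Table 1 event, each one attainable and the one for oxygen below 100%, and say that it is judged against Table 1. Keep it, because it is the more sensitive check early on for the 5% events.

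Add a confidential comparison by coded arm, prepared by the trial statistician for the DMEC alone, that can also call an emergency meeting. Leave its cut-off to the DMEC.

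The change takes a sentence or so in the protocol and an entry in the DMEC charter, and it uses data already recorded on the case report forms. The real cost is false alarms: z ≥ 2 on all nine events gives about an 18–19% chance of at least one unneeded meeting per look if events are independent, and more over repeated looks. The DMEC may therefore prefer a stricter cut-off or restrict the comparison to key events such as death and tachycardia. A false alarm costs a meeting; it does not stop the trial.
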